#### Secondary outcome measures:

- Hemoglobin A1c at baseline, 12 and 24 week follow-up visits
- Percent time of day in hypoglycemia, euglycemia, or hyperglycemia
- Glycemia variability (interstitial glucose rate of change)
- Marked hyperglycemia index
- GCSI, PAGI-SYM, and PAGI-QOL scores at baseline, 12, and 24 week follow-up visits
- Maximal volume of water and Ensure® consumed during satiety tests at baseline, 12 and 24 week follow-up visits
- Percent tachygastria, bradygastria, and normal 3 cpm activity during EGG testing at baseline, 12 and 24 week follow-up visits
- Vagal cholinergic and sympathetic adrenergic functions at baseline, 12 and 24 week follow-up visits

### 8.3 Statistical issues

The goals of this pilot study are to assess the safety, feasibility, and potential for efficacy of RT-CGM as an adjunct to SMBG in conjunction with insulin pump therapy to produce improved glycemic control in a small sample of diabetic patients with gastroparesis. The findings are intended to provide the foundation

for determination of whether a large multicenter randomized, controlled efficacy trial of RT-CGMS as an adjunct to SMBG in conjunction with insulin pump therapy vs. conventional diabetes management should be conducted in diabetic patients with symptomatic gastroparesis. The current study will provide valuable pilot data to inform the design of an efficacy trial.

As noted above, the primary safety outcome measure for our study is the weekly frequency of mild, moderate and severe hypoglycemic episodes. There is very limited (published or from other sources) information on the frequency of mild, moderate and severe hypoglycemic events in tightly controlled diabetic gastroparesis. Thus, for planning purposes, we relied upon a consensus of the clinical experiences of the investigators ([name], [name], and [name]) for estimates needed for the statistical design of this pilot study:

- Assumed mean weekly mild to moderate hypoglycemic episodes by SMBG: 0.6
- Assumed SD for weekly mild to moderate hypoglycemic episodes by meter glucose: 0.8
- Assumed intra-class correlation between baseline and on-treatment weekly mild, moderate and severe hypoglycemic episodes by meter glucose: 0.6
- Estimated variance of change from baseline (a minimum of 4 weeks up to 16 weeks) to on-treatment (24 weeks) mean weekly mild, moderate and severe hypoglycemic episodes (estimated from SD and intraclass correlation, accounting for 3:1 ratio of on-treatment to baseline period).

We planned the study to test the safety hypothesis that, compared to a minimum of 4 weeks up to 16 weeks of baseline treatment, any increase in mean weekly mild, moderate and severe hypoglycemic events during approximately 24 weeks of insulin pump treatment and RT-CGM was no larger than 35%. Using a one-sample equivalence z-test and assuming one-sided Type I error of 0.05, power =0.9, expected percent increase from baseline to on-treatment=0%, and equivalence limit of 35% (0.6 vs. 0.81 episodes per week), the calculated sample size was N=37. The method of calculation and software used are as follows:

- Method for sample size calculation: One sample test for equivalence (Chow, Shao and Wang, Sample Size Calculations In Clinical Research, Taylor & Francis, NY, 2003: p.52-53)23
- Software: Centre for Clinical Trials, Chinese University of Hong Kong24  
[http://www.cct.cuhk.edu.hk/stat/mean/osm\\_equivalence.htm](http://www.cct.cuhk.edu.hk/stat/mean/osm_equivalence.htm)

We increased the target sample size approximately 10% to N=40 patients to allow departures from assumptions. In addition, we plan to review safety data only with the DSMB when approximately N=10 patients have completed the study. The DSMB will advise on whether or not it is safe to proceed towards the full sample size of 40 patients.

An important, but secondary, efficacy outcome is reduction in hemoglobin A1c. However, if we assume that 25% (10 patients) do not achieve good glycemic control (hemoglobin A1c >7% at 12 and 24-weeks), the confidence limits on the actual proportion not achieving good control with 40 patients will be wide with a half-width of  $\pm 16\%$ . A sample size of 40 will provide adequate power to detect clinically meaningful changes in some measures of gastroparesis symptoms, quality of life, or on measures of gastric motor and sensory and autonomic function in this pilot study; however, a larger, study with a control group would be needed to provide evidence of efficacy. A 25% reduction in mean from a baseline GCSI score of  $27 \pm 15$  to  $20 \pm 15$ , with a sample size of 40, can be detected with >99% power, again assuming a Type I error of 0.05 and a modest intra-class correlation between baseline and follow-up GCSI measures. Comparisons within GLUMIT-DG subgroups will have limited statistical power; for example, we will compare Type 1 versus Type 2 diabetics for indications of differential outcomes,

however, the power for such comparisons will be low -- only 57% power for the primary hypoglycemic outcome measure with equal numbers of Type 1 or type 2 diabetics and less power if the numbers are unequal.

Questions of efficacy and subgroup comparisons for differential responses are best addressed in the context of a larger multicenter, randomized, controlled trial; however, the GLUMIT-DG pilot study will provide key information on variability in outcome measures at baseline and over time, and on the potential effect sizes - this information is not currently available for other sources and is needed to inform trial design.

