### Study duration – per patient

- A minimum of 4 weeks and up to 16 weeks of screening and baseline assessments prior to enrollment
- 24 weeks of open label treatment and follow-up after enrollment

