### 3. Study Design

#### 3.1 Design overview

GLUMIT-DG is a multicenter, uncontrolled open label treatment study assessing the safety, feasibility, and potential efficacy of RT-CGM as an adjunct to self monitoring blood glucose (SMBG) in conjunction with insulin pump therapy for patients with type 1 or type 2 diabetes and gastroparesis. Participants will include patients enrolled in GpCRC studies (e.g., Gastroparesis Registry, Gastroparesis Registry 2 Study) qualifying for GLUMIT-DG and other patients with diabetes and gastroparesis referred to study physicians, or patients from the investigators' clinics. Twenty patients with type 1 diabetes and twenty patients with type 2 diabetes will be enrolled into GLUMIT-DG study. Screening for eligibility, collection of baseline data, iPro CGM training for baseline glycemic assessments, and the run-in period for real-time continuous glucose monitoring (RT-CGM) training with the insulin pump will span up to 16 weeks after obtaining informed consent for participation in the study. After successful completion of the run-in period, patients will be enrolled in the study and use RT-CGM coupled with insulin pump therapy to optimize glucose levels while determining the frequency of hypoglycemic events for 24 weeks. After study completion, patients will be given the option of returning to or participating in the Gastroparesis Registry 2 Study. A schematic of the study design is presented below:

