### 5.1 Visit schedule overview

The patient-related activities of the GLUMIT-DG study can be divided into 3 phases:

- **Screening Phase:** Screening to determine eligibility and receive training on the use of an iPro which is a CGM used for retrospective analysis of CGM results. While wearing the device the subject is blinded to their sensor glucose values. This period is so that the subjects can demonstrate a willingness to wear a sensor, gain proficiency in inserting a sensor, and provide the study baseline data of their CGM readings (retrospectively). This will occur over 2-8 weeks and include 2 visits for gastric related testing as well as iPro training. To progress in the study the subject will need to have at least 216 hours of iPro readings.
- **Run-in Phase:** Initiation of insulin pump training and training in the use of real-time CGM (4 visits over a minimum of 2 weeks up to a maximum of 8 weeks)
- **Follow-up Phase:** Study treatment to assess the safety of using RT-CGM as an adjunct to SMBG-guided insulin pump therapy over 24 weeks (6 visits)

The visit and data collection schedule described below in detail is summarized in Appendix 10.2

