### 5.3 Screening visits and iPro training

**Screening visit 1:** The patient should be in a fasting state (no food or drink except up to 120 mL (4 oz) of water after midnight the night before) for this visit. The patient will sign the GLUMIT-DG consent at or prior to screening visit 1 and will undergo a history and physical examination to identify other illness and contraindications for participation. In addition, blood will be drawn to measure their hemoglobin A1c level. A patient's hemoglobin A1c level must be 8.0% or higher in order to be eligible for this study. Laboratory test results that need to be recorded from chart review or obtained as part of screening include: complete blood count (CBC): white blood cells, red blood cells, hemoglobin, and platelets; a comprehensive metabolic panel: sodium, potassium, chloride, carbon dioxide, calcium, glucose, blood urea nitrogen (BUN), creatinine, albumin, total protein, alanine aminotransferase (ALT), aspartate aminotransferase (AST), and bilirubin; and thyroid stimulating hormone (TSH). The Patient Assessment of Upper Gastrointestinal Disorders - Quality of Life (PAGI-QOL) and the Patient Assessment of Upper Gastrointestinal Disorders - Symptom Severity Index (PAGI-SYM) questionnaires will also be completed as well as the Baseline Medical History and Physical Examination forms.

**iPro training:** At a clinic visit as early as possible during the screening phase, patients will be seen by a diabetes educator to undergo training on measuring their interstitial glucose levels using the iPro. The iPro involves wearing a sensor device, which has a needle that is inserted in the subcutaneous tissue to continuously measure blood glucose levels. The sensor is calibrated according to blood glucose results taken from finger sticks. This is a device that collects interstitial glucose readings, but the readings are not displayed to the patient, so no insulin dose decisions are made based on CGM readings. Patients will measure their blood glucose levels using a standard finger stick method and will be required to do so 4 times daily using a glucose meter. During this period, patients will continue to take their regular diabetes medications or insulin treatment including those who already wear an insulin pump. This iPro data will not be used for adjustment of diabetes therapy since the patient cannot see the data.

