#### 5.4 Run-in visits with insulin pump training

After successful completion of iPro (or iPro2) training, patients will return for four weekly visits, for a minimum of two weeks up to an 8-week learning period to receive training on the usage of an insulin pump coupled with RT-CGM. Participants will be trained on how to use a computer to send the data gathered by the RT-CGM, glucose meter and insulin pump to their study physician and diabetes educator. During the run-in period insulin pump infusion parameters will be adjusted to optimize regulation of blood glucose levels, using information from both their SMBG and from trend analysis of the RT-CGM which will be used only as an adjunct to SMBG.

**Run-in visit 1:** Participants will receive instruction on use of the RT-CGM, including the uploading of the data using the CareLink system as well as instructions on glycemia management using their SMBG which will be supplemented with the trend identification using the RT-CGM. The RT-CGM has a feature known as “REAL-Time Alarms” which will be set to warn patients when their glucose levels are very low or very high. The hypoglycemic alarm threshold will be set at 80 mg/dL and the hyperglycemic alarm threshold will be set at 240 mg/dL. The low glucose snooze will be set between 15-20 minutes to allow time to observe the effect of treatment for the hypoglycemia, and the high glucose snooze will be set to 1-2 hours to allow time to observe the effects of a corrective dose of insulin. They will be taught how to calibrate their RT-CGM using 2-4 glucose readings each day, obtained when there is a low rate of glucose change, as indicated by an absence of rate of change arrows. The subjects will be instructed to not make any insulin dose decisions based on the RT-CGM glucose reading without obtaining a blood glucose measurement using their glucose meter. Insulin doses may be modified based on the glucose rate of change, as was done during the JDRF and STAR 1 and STAR 3 trials. (See package insert for instructions for use of CGM)

**Run-in visit 2:** This visit should be planned within a week after the first run-in visit. Patients will be taught insulin infusion pump mechanics and will be started on an insulin pump filled with saline. The purpose of filling the pump with saline is to ensure that the patient can tolerate wearing it before it is filled with insulin.

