**Run-in visit 3:** Patients will stop previous diabetes treatment and insulin administration with the pump will be initiated according to predetermined insulin dose parameters. For those patients who entered the study using an insulin pump, parameters will be adjusted as per their meter blood glucose readings using their RT-CGM readings as adjunctive information. Carbohydrate to insulin ratios, insulin sensitivity, insulin on board (3 to 5 hours), and glycemic targets will be established by the study staff. Patients will be instructed to only use the bolus wizard feature of the pump when delivering insulin doses for meals to ensure the proper amount of insulin is delivered. Due to the presence of gastroparesis, meal boluses for control of postprandial hyperglycemia combination meal boluses using a standard bolus and square wave bolus may be utilized with adjustments made based on post prandial glucose trends. This approach is aimed at minimizing a mismatch in insulin bolus administration and nutrient absorption due to delayed and possibly erratic gastric emptying. In addition to intensive education on glycemic control, participants will be instructed in depth on symptoms and signs of hypoglycemia and steps to correct it without caloric over replacement to avoid rebound hyperglycemia.

**Run-in visit 4:** Patients will review their RT- CGM results and receive additional education on glycemia management. They will also be taught how to use glucose trends as displayed by the RT-CGM as adjunctive information to their SMBG to modify their insulin doses and to ingest carbohydrates if the RT-CGM identifies a risk of hypoglycemia, if it is confirmed by a meter glucose reading. In addition, blood will be drawn to measure their hemoglobin A1c level.

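### The 4 to 16 week baseline of the primary safety comparison includes the run-in, so weeks on the study treatment count as control

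*Protocol*

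**What the plan says.** Section 8.3 states the safety hypothesis that any increase in mean weekly hypoglycaemic events over about 24 weeks of pump treatment and RT-CGM, "compared to a minimum of 4 weeks up to 16 weeks of baseline treatment", is no larger than 35%. The sample-size part of the synopsis gives the same baseline window.

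The synopsis describes everything before enrollment with the same limits: "A minimum of 4 weeks and up to 16 weeks of screening and baseline assessments prior to enrollment". Section 5.1 divides that time into two phases. For screening it says "This will occur over 2-8 weeks and include 2 visits for gastric related testing as well as iPro training"; for the run-in it gives "4 visits over a minimum of 2 weeks up to a maximum of 8 weeks". Section 3.1 also counts the run-in within the pre-enrollment time: "the run-in period for real-time continuous glucose monitoring (RT-CGM) training with the insulin pump will span up to 16 weeks".

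Therapy differs between the two phases. Of the iPro weeks in screening, Section 5.3 says "During this period, patients will continue to take their regular diabetes medications or insulin treatment including those who already wear an insulin pump". In the run-in (Section 5.4), RT-CGM with alarms starts at visit 1, a saline-filled pump at visit 2, and at visit 3 "Patients will stop previous diabetes treatment and insulin administration with the pump will be initiated according to predetermined insulin dose parameters". The same section adds: "During the run-in period insulin pump infusion parameters will be adjusted to optimize regulation of blood glucose levels". Enrollment comes after all of this.

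**The concern.** The comparator in a test of whether pump plus RT-CGM raises hypoglycaemia should be time without that treatment. As the window is written, it takes in weeks on pump insulin, including the start-up and titration weeks. An episode caused by starting the pump then raises the baseline rate instead of counting against the treatment.

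If those weeks have a raised rate, the measured increase shrinks towards zero and the test leans towards a finding of safety. Safety is the principal objective, and Section 8.3 says the results will inform whether a large randomized trial is done. The monitoring calculation in Section 8.4, which prompts a DSMB vote when the lower confidence limit on the increase from baseline exceeds 35%, would be blunted in the same way.

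**Working it through.** **1. What the window can contain.** Screening 2 to 8 weeks plus run-in 2 to 8 weeks gives 4 to 16 weeks, exactly the stated baseline. Screening alone cannot exceed 8 weeks, so a 16-week baseline is possible only if the run-in is counted.

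**2. The protocol's own variance.** Inputs from the synopsis: SD 0.8, intra-class correlation 0.6, period ratio 3:1.

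0.8² × (1 + 1/3 − 2 × 0.6 × √(1/3)) = 0.64 × 0.6405 = 0.41

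This reproduces the stated 0.41. A 3:1 ratio against 24 weeks means an 8-week baseline. The stated window gives 24/4 = 6:1 to 24/16 = 1.5:1, so window and ratio disagree.

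**3. Share of the baseline on pump insulin (f).** The protocol does not give it. Assumed visit timing:
- 2 + 2 weeks, four evenly spaced run-in visits: visit 3 falls at 4/3 weeks, leaving 2/3 week on pump insulin; f = (2/3)/4 = 0.17.
- 8 + 8 weeks, weekly visits: visit 3 falls about 2 weeks into the run-in, leaving 6 weeks; f = 6/16 = 0.375.

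Other combinations go outside this range: 8 weeks of screening with a 2-week run-in gives (2/3)/10 = 0.07, and 2 weeks of screening with an 8-week run-in gives 6/10 = 0.60.

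**4. Dilution.** Let r be the true relative increase, and assume pump-insulin run-in weeks have the follow-up rate. The observed ratio is (1 + r)/(1 + f r), and the true increase needed to observe 35% is r = 0.35/(1 − 1.35 f).

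| f | True +35% is observed as | True increase needed to observe +35% |
|---|---|---|
| 0 | +35% | +35% |
| 0.17 | 1.35/1.058 = 1.28, so +28% | 0.35/0.775 = +45% |
| 0.375 | 1.35/1.131 = 1.19, so +19% | 0.35/0.494 = +71% |

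**5. Chance of wrongly passing at a true +35%.** Inputs: N = 40, variance of change 0.41, margin 0.21 episodes per week (0.81 − 0.6), one-sided 5%. The standard error is √(0.41/40) = 0.101. The expected observed difference is 0.21(1 − f), and the test passes when the estimate is below 0.21 − 1.645 × 0.101 = 0.043.
- f = 0: expected difference 0.210, z = −1.645, chance 5%.
- f = 0.17: expected difference 0.175, z = −1.30, chance about 10%.
- f = 0.375: expected difference 0.131, z = −0.87, chance about 19%.

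Variance and margin are held at their planned values. Whether N = 37 follows from the stated inputs is a separate question and is not used here.

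**The case against.** The strongest reply is that baseline was meant to be the iPro weeks. The synopsis visit schedule places the baseline assessment with iPro learning, Sections 3.2 and 5.1 say those weeks supply baseline glycaemic or CGM data, and the 3:1 ratio fits an 8-week screening phase. This shows that the text conflicts with itself. It does not rescue the stated window: nowhere is the primary hypoglycaemia rate restricted to those weeks or the run-in excluded, and Section 3.3 attaches the word baseline to run-in RT-CGM data. An analysis plan might settle the point, but the protocol already fixes a window that is wrong for its purpose.

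Three limits on size and direction stand. Between run-in visits 1 and 3 patients use RT-CGM on prior therapy. Alarms might prevent episodes, and extra meter checks might reveal more, so those weeks could move the baseline rate either way. Patients who entered on a pump have less contrast between periods. The equal-rate assumption is also untested.

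A reader might infer that half of the baseline is treated (2 of 4 or 8 of 16 weeks), so that a true increase of 108% would pass as 35%: 0.35/(1 − 0.675) = 1.08. Section 5.4 does not support that reading, because it treats the whole run-in as full intervention when pump insulin starts only at visit 3.

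Nor are start-up events lost to safety review. The schedule in Appendix 11.2 covers adverse events in the run-in, and Section 7.1 makes severe hypoglycaemia an SAE at any time in the study. What is affected is the primary comparison.

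**Conclusion.** The point holds. The stated baseline for the primary safety comparison can be filled only by counting the run-in, and the run-in contains the study treatment. It also contradicts the 3:1 ratio and the passages that place baseline data in the iPro weeks.

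At the shortest and longest windows, under the assumed visit spacing and equal rates in pump-insulin run-in weeks and follow-up, the 35% limit behaves like a limit of about 45% to 71%, and the 5% error becomes about 10% to 19%. The effect is larger when screening is short and the run-in long, and smaller in the reverse case. A higher start-up rate would enlarge it. The documents do not support treating the direction as certain for the RT-CGM-only weeks or for patients already on a pump. The need to correct the window does not depend on the exact size.

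**What to change.** Define the primary baseline, for the Section 8.3 test and for the DSMB calculation in Section 8.4, as the meter-glucose weeks on prior therapy before run-in visit 1. Report run-in episodes as a separate on-treatment safety period, with a sensitivity analysis that adds the pump-insulin run-in weeks to the treatment period. Correct the baseline window and the 3:1 ratio in the synopsis and Section 8.3, and restate the variance of change.

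No new measurements are needed, because four meter tests a day are already required during iPro use in screening. However, CareLink upload is first taught at run-in visit 1, so the sponsor should confirm that screening meter data reach the analysis database.

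The real cost is precision, since the baseline becomes 2 to 8 weeks. Under the protocol's own scaling, with SD 0.8 taken to describe an 8-week mean and the correlation kept at 0.6:
- 8 weeks: 0.41, unchanged.
- 4 weeks: 0.64 × (2 + 1/3 − 1.2 × √(2/3)) = 0.87.
- 2 weeks: 0.64 × (4 + 1/3 − 1.2 × √(4/3)) = 1.89, about 4.6 times the planned value.

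At 0.6 episodes per week, a 2-week baseline yields only 1.2 expected episodes per patient. All available screening meter data should therefore be used, and the precision to be expected with 40 patients should be stated.

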### Sample size and statistical analysis of primary outcome

- A total of 40 patients will be enrolled in this pilot study
- Rationale for sample size
  - Primary safety outcome: weekly frequency of mild, moderate, or severe hypoglycemic episodes by discrete glucose meter values and/or a reference blood glucose level if the subject is seen in a hospital (emergency room)
  - Assumed mean weekly mild, moderate, or severe hypoglycemic episodes by discrete glucose values: 0.6
  - Assumed SD for weekly mild, moderate, or severe hypoglycemic episodes by discrete glucose values: 0.8
  - Assumed intra-class correlation between baseline and on-treatment weekly mild, moderate, or severe hypoglycemic episodes by discrete glucose values: 0.6
  - Estimated variance of change from baseline (a minimum of 4 weeks up to 16 weeks) to on-treatment (24 weeks) mean weekly mild, moderate, or severe hypoglycemic episodes (estimated from SD and intraclass correlation, accounting for 3:1 ratio of on-treatment to baseline period lengths): 0.41
  - Type I error: 0.05 (1-sided for equivalence)
  - Power: 0.9
  - Expected percent increase from baseline in mean weekly mild, moderate, or severe hypoglycemic episodes during the treatment period with RT-CGM while using the

- glucose pump: 0%
- Equivalence limit (maximum percent increase in mean weekly mild, moderate, or severe hypoglycemic episodes): 35% (0.6 vs. 0.81 episodes per week)
- Method for sample size calculation: One sample test for equivalence (Chow, Shao and Wang, Sample Size Calculations In Clinical Research, Taylor & Francis, NY, 2003: p. 52-53)
- Software: Centre for Clinical Trials, Chinese University of Hong Kong -- [http://www.cct.cuhk.edu.hk/stat/mean/osm\\_equivalence.htm](http://www.cct.cuhk.edu.hk/stat/mean/osm_equivalence.htm)
- Calculated sample size: N = 37

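### The safety hypothesis limits only an increase in hypoglycaemia, but the test and sample-size method named for it are two-limit equivalence

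*Protocol*

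**What the plan says.** The hypothesis is bounded on one side. Section 8.3 plans to test that a rise over the baseline period in "hypoglycemic events during approximately 24 weeks of insulin pump treatment and RT-CGM was no larger than 35"%. The synopsis defines the limit in the same direction: "Equivalence limit (maximum percent increase in mean weekly mild, moderate, or severe hypoglycemic episodes): 35% (0.6 vs. 0.81 episodes per week"). Section 8.4 also monitors in that direction only. The DSMB is asked to discuss and vote if the lower 95% confidence limit on the percent increase exceeds 35%.

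The named test belongs to a different hypothesis. Section 8.3 continues: "Using a one-sample equivalence z-test and assuming one-sided Type I error of 0.05, power =0.9, expected percent increase from baseline to on-treatment=0"%. The synopsis gives "Method for sample size calculation: One sample test for equivalence" and cites a textbook equivalence method and an online equivalence calculator; section 8.3 repeats both. The error rate is given as "Type I error: 0.05 (1-sided for equivalence").

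The result is N=37, raised to 40 to allow for departures from the assumptions. The protocol writes no lower limit, no formal null hypothesis and no rule for the final safety conclusion.

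**The concern.** An equivalence test concludes only when a change beyond the limit is excluded in both directions. The safety question here has one direction: is hypoglycaemia more than 35% more frequent on treatment? A fall in hypoglycaemia is no safety problem, and nothing in the protocol treats it as one. If the named test became the decision rule, patients whose episodes became rarer would count against the safety conclusion, and part of the power of a 40-patient pilot would be spent on excluding a decrease that nobody needs to exclude.

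The mismatch could be a loose use of the word equivalence for a one-sided comparison. The arithmetic behind N=37 shows whether it is.

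**Working it through.** **Inputs** (synopsis, sample-size section; section 8.3): one-sided alpha 0.05, power 0.9, baseline mean 0.6 episodes per week, variance of the change 0.41, expected change 0, limit 35%, written as 0.6 against 0.81, that is 0.81 − 0.6 = 0.21 episodes per week. Calculated N=37, target N=40.

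**1. Reproducing N=37.** With sigma² the variance of the change, delta the limit and a true change of zero:

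- Equivalence, two limits: n = (z(1−alpha) + z(1−beta/2))² × sigma² / delta², with both z values 1.645.
- One-sided non-inferiority: n = (z(1−alpha) + z(1−beta))² × sigma² / delta², with z values 1.645 and 1.282.

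| delta (episodes/week) | Equivalence | One-sided |
|---|---|---|
| 0.21 (the stated limit) | (1.645+1.645)² × 0.41/0.21² = 100.6, so 101 | (1.645+1.282)² × 0.41/0.21² = 79.6, so 80 |
| 0.35 | (1.645+1.645)² × 0.41/0.35² = 36.2, so **37** | (1.645+1.282)² × 0.41/0.35² = 28.7, so 29 |

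With the stated alpha, power and variance, 37 appears in one cell only. This shows two things. The two-limit formula was used, because the one-sided formula with the same entries gives 29. And the limit entered was 0.35 episodes per week, not the stated 0.21; 0.35 is 58% of the 0.6 baseline mean (0.35/0.6).

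**2. Chance of concluding safety with 40 patients.** SE = sqrt(0.41/40) = 0.1012. For a true change d in episodes per week:

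- One-sided: Phi((delta − d)/SE − 1.645).
- Equivalence with limits ±delta: Phi((c − d)/SE) − Phi((−c − d)/SE), where c = delta − 1.645 × SE. This gives c = 0.0435 for delta 0.21 and c = 0.1835 for delta 0.35.

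| True change | d | One-sided, 0.21 | Equivalence, ±0.21 | One-sided, 0.35 | Equivalence, ±0.35 |
|---|---|---|---|---|---|
| 0% | 0 | 67% | 33% | 96.5% | 93% |
| −20% | −0.12 | 95% | 17% | over 99% | 73% |
| −35% | −0.21 | 99% | 4% | over 99% | 40% |

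**3. What the lower limit buys.** At a true 35% increase (d = +0.21) with the 0.21 limit, the one-sided test wrongly concludes safety 5% of the time. The equivalence test does so with probability Phi(−1.645) − Phi(−2.505) = 0.050 − 0.006 = 0.044, about 4%. The lower limit adds almost no protection.

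**The case against.** The strongest reply is that the protocol never says a decrease would count as failure. The hypothesis, the definition of the limit, the one-sided error and the DSMB trigger all look only at an increase. The equivalence test is named only in the planning calculation and its method citation, and the final rule may stand in an SAP that is not shown. All of this stands. A reader might infer that a real fall in hypoglycaemia would make the trial fail to show safety. The documents do not support that: the loss arises only if the named test is applied with a symmetric lower limit, and even then it is a lower probability of concluding safety, not certain failure.

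A reader might also infer that the loss is the same whatever the limit. It is not. At no change it is 34 percentage points with 0.21 per week and about 3.5 with 0.35.

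Nor do the documents say that a fall is expected. The planning value is a 0% change. The remark in section 5.7 that dual-wave boluses lower the chance of hypoglycaemia compares ways of delivering a bolus, not treatment with baseline. The 20% and 35% falls in the table are illustrations.

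Finally, the equivalence formula asks for more patients than the one-sided one at either limit, so the choice does not make a false conclusion of safety more likely. This too stands, and it makes the point less serious. It does not remove the contradiction. An SAP that followed the protocol's named test would carry the unwanted lower limit forward, and one that used a one-sided test would depart from the protocol.

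**Conclusion.** The protocol pairs a one-directional hypothesis with a two-limit test and a sample size computed for that test. This is more than loose wording, because N=37 carries the beta/2 term.

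The cost is conditional on applying the test with symmetric limits. At the stated limit of 0.21 per week, the chance of concluding safety drops from 67% to 33% at no change, and from 99% to 4% at a true 35% fall. At 0.35 per week it drops from 96.5% to 93%, and from over 99% to 40%.

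The correction does not rescue the planned power. At N=40 and the stated limit, a one-sided test has about 67% power, and 90% would need 80 patients. Most of the shortfall from 90% comes from the separate mismatch between 0.35 and 0.21, not from the choice of test.

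The figures take the variance of 0.41 as the protocol states it; its derivation from the SD and correlation was not confirmed. They use a normal approximation and treat the 35% limit as a fixed 0.21 per week, without allowing for uncertainty in the baseline mean.

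**What to change.** In section 8.3 and the synopsis:

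- Replace the one-sample equivalence test and equivalence limit with a one-sided non-inferiority test at alpha 0.05. Safety is concluded if the upper one-sided 95% confidence limit on the percent increase in mean weekly episodes is below 35%, with no lower limit.
- Restate the power at N=40 for the stated limit of 0.21 episodes per week, using z(1−beta) in place of z(1−beta/2). It is about 67%, not 90%.
- State separately that N=37 follows only if 35% was entered as 0.35 episodes per week, so that readers do not take it as the sample size for 0.6 against 0.81.

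The cost is a change of wording in two places and a restated power figure, which will be visibly lower than the 90% now given. It needs no new patients, visits or data. Alpha stays as it is, and no change in N is asked for.
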